#### Other outcomes

▪ HSA and caregiver-perceived barriers and facilitators to caregiver compliance with urgent referral recommendations▪ Direct and indirect costs to caregivers of planned and unplanned re-consultations and urgent referrals to any type of health facility (i.e., health centers, community/rural and district hospitals)▪ HSA and caregiver attitudes towards the SL eCCM App and the intervention experience

### Recruitment

Recruitment was coordinated from Luke International Offices in Mzuzu, Mzimba North District. HSAs were identified from village clinics listed on the Demographic and Health Information System 2 (DHIS 2 http://www.dhis2.org/) database (a repository for centralizing health data) that is used widely across Africa [38]. Guidance was sought from district-level Ministry of Health (MoH) officials (e.g., District Health Officer, District Environmental Health Officer, IMCI coordinator) in Rumphi and Nkhata Bay to identify the status of listed village clinics (i.e., whether an HSA is in situ) and how to approach/access HSAs. A reserve of HSAs was identified in case any identified village clinics are inactive, or HSAs do not wish to participate. HSAs were to be invited to participate by the local study team, either in person or over the telephone. Caregivers and their children were identified and enrolled consecutively by HSAs as they presented to village clinics. Based on average HSA recruitment rates during the feasibility study of 10 children per HSA each week, we anticipated that 8000 children would be enrolled into the trial.

## Assignment of interventions

### Randomization, allocation and blinding

HSAs were stratified by geography into six clusters by the local study team and each cluster was given a number between 1 and 6 Using computer-generated simple randomization techniques, each of the six clusters was randomized to the sequence and timing at which they crossed over from the control to the intervention (Fig. 3) [39]. Clusters were randomized once allocated to geographic clusters. Caregivers and their child were allocated to the control or intervention by chance, depending on the time that they presented to village clinics. Due to the nature of the intervention, neither trial participants nor the trial team were able to be blinded to assignments.

### Trial procedures

#### Training workshops

HSAs attended two 1-day training workshops where they learnt how to use the SL eCCM App and became familiarized with study procedures with other HSAs in the same cluster. At the first training workshop HSAs were taught how to operate the smartphone (e.g., turning device on/off; navigation to the SL eCCM App); use the SL eCCM App (e.g., navigate through clinical questions and assessment items; were taught procedures for uploading data onto the central database, using the embedded breathing rate counter) and follow study procedures (i.e., how to recruit and obtain verbal consent from caregivers, and record data in the SL eCCM App and paper-CCM in parallel). At the end of the first training workshop a mobile phone without the SL eCCM App was issued to HSAs, allowing them to become familiar with the device. The App was removed from devices at this time to prevent HSAs using it to treat children during the control phase.

The second workshop was a “refresher” session, conducted 1–2 weeks before each cluster crossed over to the intervention (i.e., paper-CCM + SL eCCM App). The SL eCCM App was downloaded onto the mobile phones assigned to HSAs, ready for the intervention phase. Material covered in the first workshop was also revised. To consolidate learning and encourage compliance with study procedures, clinical vignettes were conducted to simulate study procedures expected to be undertaken by HSAs in the intervention phase.

To ensure a manageable ratio of trainers to HSAs, training workshops were limited to a maximum of 20 HSAs. Training workshops were led by the study team in English, and included a team member fluent in the primary language spoken by participants who could facilitate communication. During the blocked-out time periods allocated to training workshops, HSAs continued to use paper-CCM as per standard practice, but were not able to enroll children during this transitory stage (prevented by removing all study materials from village clinics).

## Data collection

### Baseline

#### Control

Paper-CCM was used to assess and treat children for between 2 and 7 weeks (dependent on clusters’ assigned sequence from randomization), as per standard practice. Facilitated by the Sick Child Form, patient data routinely collected by HSAs through a series of questions and physical examinations was recorded in the village clinic register and included: demographic data (i.e., child and caregiver name, child date of birth, relationship of caregiver to child, physical address); the presence and duration of “sick” signs (i.e., diarrhea for less than 14 days without blood in stool, fever for less than 7 days, red eye for less than 4 days, fast breathing) and “danger” signs (i.e., cough for 21 days or more, diarrhea for 14 days or more, blood in stool, fever lasting for 7 days, convulsions, not able to feed or drink anything, vomits everything, red eye for 4 days or more, red eye with visual problem, chest recession, very sleepy or unconscious, palmar pallor, red/yellow on MUAC tape, swelling of both feet); treatment decision (i.e., urgent referral or treat at home and advise on homecare, including when to return for follow-up) and medication dispensed (e.g., antibiotics, oral rehydration therapy).

#### Intervention

After HSAs in each cluster completed their allocated time in the control and the second training workshop, they transitioned to using the SL eCCM App in addition to paper-based CCM for between 2 and 7 weeks. The same patient data recorded in the control was collected and recorded concurrently in the SL eCCM App and village clinic register. Dual-use and double-data entry were necessary due to functional limitations of the SL eCCM App and because completion of the village clinic register is mandatory for monthly aggregation of cases for country-level disease surveillance purposes. During technical malfunctions (e.g., software bugs, power failures, etc.) that prevented use of the App, or scenarios where caregivers could not be consented, HSAs temporarily reverted to paper-CCM only. HSAs dispensed treatment using recommendations prompted by the SL eCCM App, but could elect to follow recommendations of paper-CCM where they strongly disagreed with the App’s recommendations. Use of the breath count feature to measure RR was encouraged, but HSAs could choose to use the stopwatch (as per standard practice) if they preferred.

### Follow-up

Two weeks following enrollment, caregivers recruited in both the control and intervention phases were contacted by the study team via the mobile telephone number (provided at recruitment), or in person (if they did not provide a number, or were unreachable on the number provided). They were asked by one of the Malawian study team for details of: treatment recommendation given by HSAs at the index visit; re-attendances at village clinics, presentations to higher-level facilities and hospitalizations of their child in the 7 days following the index visit. Since identification of patient records at sites is anticipated to be cumbersome due to poor medical administrative infrastructure [15, 40], information provided by caregivers was used to direct the study team to sites where a record of the patient visit was most likely to be available. Caregiver-reported data will be cross-referenced with data abstracted from patient records to determine the trustworthiness of gathering data from village clinics and higher-level health facilities.

The study team systematically visited participating village clinics and higher-level health facilities within the catchment area of recruiting village clinics to retrospectively obtain the following from patient records: HSAs’ treatment decisions and scheduled follow-up visits with caregivers at the index visit (i.e., urgent referral, treated at home/advice to caregiver); dates of re-attendances at village clinics (including signs/symptoms at presentation and medications administered, if any); dates of attendances and hospitalizations (including diagnoses and medication administered, if any). Follow-up data was recorded on a Case Report Form (CRF).

A subgroup of caregivers, recruited in both the control and intervention phases, who returned to village clinics or who took their child to a higher-level health facility (irrespective of whether an “urgent referral” recommendation was given at the index visit), were asked to complete a Patient Costs Questionnaire (PCQ). The survey was adapted from the Cooking and Pneumonia Study (CAPS) implemented in Malawi [41] and collected sociodemographic details (e.g., level of education, marital status, occupation), financial (e.g., cost of transportation, medication) and time-related (e.g., duration of travel) costs associated with seeking subequent health care for their child. Where practical, survey data was collected from caregivers over the telephone, or, obtained in person in the community with the assistance of the recruiting HSA. Because we anticipated mixed literacy levels among the patient population, the survey was completed either by the caregiver, or by a member of the study team fluent in the local language, who read the questions and scribed on behalf of caregivers. A convenience sample of enrolled HSAs and caregivers from each cluster participated in a semi-structured interview 1–2 weeks after the intervention (HSAs) or recruitment (caregivers), respectively. One-to-one interviews were conducted in person (or depending on location/availability of caregivers, over the telephone) by a member of the study team fluent in the primary language of participants. This interview format was selected due to the influence that cultural factors (e.g., collectivism, gender and sociodemographic inequities) could have on openness of communication in group interviews [42]. Tailored, semi-structured topic guides were used to facilitate interviews and included questions relating to perceptions of the barriers and facilitators to caregiver compliance with urgent referral recommendations and the perceived impact of the SL eCCM App. Topic guides were developed by the study team and were informed by nascent research related to challenges of accessing health care in LMICs, and from findings from focus groups held as part of the feasibility study. All interviews were audio-recorded, lasted between 30 and 40 min, and were held in private. Data collection instruments and/or interview guides can be made available upon request to the corresponding author.

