Correct identification of children requiring urgent referral is largely dependent upon CHWs’ fidelity to CCM guidelines, which has been frequently reported as suboptimal [3, 7–10]. Poor completion of relevant CCM assessment items may hinder early recognition of serious illness, reducing urgent referrals to higher-level facilities. Information about CCM-directed urgent referral rates in Malawi is limited. However, assessment of the quality of implementation of the CCM program after national scale-up in 2008 reported that CHWs on average made two urgent referrals (per 1000 children) each month [11]. Given the countries’ annual childhood mortality rates from pneumonia (23%), malaria (14%) and diarrhea (18%) [12], this suggests that many children meeting the classification for urgent referral are not being identified. Under-referral risks repeat consultations [13] for the same illness episode as well as hospitalization of those children with serious illness who are left untreated. But, due to the lack of an integrated and electronic medical record system [14, 15], it is unclear which children are brought back to village clinics because they are still unwell, and which of those admitted to hospital were urgently referred by CHWs at the index visit.

Of equal importance is that children who are urgently referred are actually taken to higher-level facilities (in other words, that the referral is completed) when advised [16, 17]. Failure to follow recommendations risks the development of chronic conditions or acute complications [18]. It is suggested that over 50% of caregivers in sub-Saharan Africa whose children are urgently referred, do not take their child for onward care [16, 19–21]. Prohibitive financial and time-related costs incurred by caregivers travelling large geographical distances to facilities [22], and mistrust in CHW “diagnoses” and treatment decisions [23, 24] have been cited as factors contributing to poor referral completion rates.

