Utilizing mobile health (mHealth) technologies (e.g., smartphones, tablets) to deliver CCM could encourage the dispensation of more appropriate treatment recommendations [25] thereby increasing urgent referral rates. Potential improvements may be underpinned by a combination of better control of how the end-user navigates through assessment questions (e.g., built-in validation rules forcing completion of relevant fields with valid data before advancing to the next field/screen) [26]; enhanced CHW motivation linked to the prestige of using advanced technology in a predominantly paper-based health care system; automated presentation of the next-steps reducing reliance on memory [27], and heightened perceived efficacy and caregiver trust in CHWs’ decisions linked to clearer explanations about the child’s condition and recommended treatment [27].

Despite the opportunities that mHealth may afford for circumventing some of the limitations of current paper-based delivery [26], there is a paucity of evidence demonstrating the comparative benefits of deploying digitized versions of CCM on health service utilization and associated patient costs. To address this evidence gap in a pragmatic cluster-randomized trial, we will evaluate the added value of an electronic CCM App (truncated to SL eCCM App) developed as part of the Supporting Low-cost Interventions For disEase control (Supporting LIFE) program. As well as contributing to the broader mHealth literature, we anticipate that trial findings will provide Malawi’s mHealth Working Group with empirical data, which can be used to inform policy regarding the opportunities to Malawi of introducing such interventions for CCM. Our hypothesis is that adding the SL eCCM App to sick child assessments will increase urgent referral rates and reduce re-consultation and hospitalization rates.

The main objectives of this trial were to determine the:▪ Added value of the SL eCCM App (used with paper-CCM) on referral, re-consultations and hospitalization rates among acutely unwell children aged under 5 years, compared with paper-CCM alone▪ Factors influencing caregivers’ decisions to comply with urgent referral recommendations▪ Direct and indirect costs to caregivers presenting to higher-level facilities and/or re-attending village clinics after the index visit when using paper-CCM and the paper-CCM + SL eCCM App

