### Sample size

We planned to recruit a total of 102 HSAs. Our sample size estimation is based on change in proportions of the primary outcomes expected pre and post intervention. Assuming an alpha of 0.05, 97 HSAs would provide 80% power for a minimum detectable rate of change between 6 and 7% in referral, re-consultation and hospitalizations (one-sided test). We assumed a 1% urgent referral rate, based on the proportion of children identified as needing to be urgently referred at clinics in a previous study conducted in Malawi [11]. As an urgent referral rate of 8% has been estimated as a reasonable consensus referral rate at clinics in sub-Saharan Africa [43, 44] that are correctly adhering to IMCI, we assumed the addition of the SL eCCM App could improve urgent referral rates close to this estimate; a 6–7% change between the control and intervention was, therefore, a conservative estimate of this assumption. Given the short trial duration and potential of perceived elevated status through smartphone ownership in this setting [45], we did not expect many HSAs to drop out. We believed that recruiting 102 HSAs would be sufficient to accommodate potential dropout, to ensure we achieved our desired sample size. Power calculations were computed using the “Power and Sample Size” option in Stata v. 13 (StataCorp, College Station, TX, USA) [46] which is appropriate for rates, specifically “*longitudinal studies, where the same cases serve as their own controls over time*” [47].

A total of 300 parents/caregivers whose children were referred to a higher-level facility or re-consulted at a village clinic completed the PCQ. It was estimated that approximately 600 children would be eligible for referral to a health care facility assuming: a 1% referral rate among 4000 children in the control group (*n* = 40), a 7–8% referral rate (change 6–7% from the initial 1% referral rate) among the same number of children in the intervention group (*n* = 300) and a 6–7% under-referral rate in the control group (*n* = 260). Considering the challenges in identifying those who were referred but did not present at a health care facility, or those who were not referred but did visit a health care facility or represented at a village clinic, and the possible withdrawal or loss to follow-up of parents/caregivers, it is estimated that at least half (*n* = 300) of the eligible cases will be followed up as part of the cost evaluation.

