We also interviewed 15 HSAs and 25 caregivers to explore barriers and facilitators to caregiver compliance with referral recommendations, as well as HSA and caregiver acceptability of the SL eCCM App. Pre-determining the number of participants needed in qualitative research is challenging since the underlying goal of achieving saturation is influenced by factors including interview type (typically one-to-one interviews foster deeper but more narrow exploration of concepts than focus groups, due to absence of exchange of opinions which broaden scope), homogeneity of interviewees, and skill of the researcher (among other things). Guest et al. indicated 12 semi-structured interviews as sufficient to attain saturation [48]. Since our approach is exploratory rather than theoretical, we believed that our target sample size would be sufficient to address our research question and accommodate any heterogeneity among either participant population.

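### The caregiver interviews on compliance with urgent referral are not selected on referral status, so first-hand caregiver evidence for that objective is likely to be thin

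*Protocol article*

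**What the plan says.** The objectives at the end of the Background section of the protocol article include "Factors influencing caregivers’ decisions to comply with urgent referral recommendations". Under Other outcomes, the matching measure is "HSA and caregiver-perceived barriers and facilitators to caregiver compliance with urgent referral recommendations".

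The Follow-up section gives the sampling rule for the interviews: "A convenience sample of enrolled HSAs and caregivers from each cluster participated in a semi-structured interview". Caregivers are interviewed 1–2 weeks after recruitment. The same section restricts the cost questionnaire to caregivers who returned to a village clinic or went to a higher-level facility. It places no comparable restriction on the interviews.

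The Sample size section gives the numbers and the first purpose: "We also interviewed 15 HSAs and 25 caregivers to explore barriers and facilitators to caregiver compliance with referral recommendations". A second purpose, in the same sentence, is to learn how acceptable both groups find the App. The number is supported by a published benchmark of 12 interviews for saturation. The qualitative paragraph of Statistical/analysis methods says that theoretical sampling is impractical because translation and transcription take time, and that the qualitative data will be triangulated with the primary outcomes.

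**The concern.** Only a caregiver whose child was urgently referred has had to decide whether to comply. The article expects such referrals to be uncommon, yet it draws the interviewees from all enrolled caregivers. Followed as written, that frame would mostly yield people who can speak about the decision only in the hypothetical. Those who were referred and did not go, who can best explain non-compliance, could be missing altogether.

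This is more than an omitted detail. The article names both a method and a frame, and neither is matched to the objective. For the cost questionnaire, in the same section, it does set a targeted frame. What is at stake is how far the interviews can explain referral completion when they are set beside the quantitative results. The randomized comparison is not affected.

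**Working it through.** **Inputs**
- Control phase: "a 1% referral rate among 4000 children in the control group", so 40 (Sample size).
- Intervention phase: 7–8% of 4000, which the article rounds to 300 (Sample size).
- Under-referred in control: 6–7% of 4000, which the article gives as 260 (Sample size).
- Total enrolment: 8000 (Recruitment).
- Caregivers interviewed: 25. HSAs interviewed: 15, of 102 planned (Sample size).
- Non-completion: the Background reports that "over 50% of caregivers in sub-Saharan Africa whose children are urgently referred, do not take their child for onward care". This is a regional background figure, not a planning value of the trial. I use 50%.

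**The plan's own figure.** 4000 × 0.01 + 4000 × 0.075 + 4000 × 0.065 = 40 + 300 + 260 = 600. This matches the article's approximate 600 children eligible for referral. The 260 were by definition not referred, so they do not count here.

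**Assumption.** The 25 caregivers are treated as resembling enrolment in referral status. The article does not state this. It is what an unselected sample would give on average.

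**Referred caregivers among 25**
- Share referred: (40 + 300)/8000 = 4.25%. With 7% or 8% in the intervention phase it is 320/8000 = 4.0% or 360/8000 = 4.5%.
- Expected number: 25 × 0.0425 = 1.06 (range 1.00 to 1.13).
- Chance of none: (1 − 0.0425)^25 = 0.34 (range 0.36 to 0.32).

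**If the sample leans to one phase**
- All from control: 25 × 0.01 = 0.25 expected.
- All from intervention: 25 × 0.07 = 1.75 to 25 × 0.08 = 2.0 expected, with a chance of none between 16% and 12%.

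**Referred caregivers who did not complete**
- Share: 0.5 × 4.25% = 2.125%.
- Expected number: 25 × 0.02125 = 0.53.
- Chance of none: (1 − 0.02125)^25 = 0.58.
- A higher non-completion rate raises the expected number, but it cannot exceed the 1.06 who were referred.

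**Against the plan's benchmark of 12 interviews**
- Unselected interviews needed to expect 12 referred caregivers: 12/0.0425 = 282.
- Enrichment needed to expect 12 among 25: (12/25)/0.0425 = 11.3-fold.

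**The HSA side**
- Referrals per HSA: 340/102 = 3.3.
- Study referrals made by 15 HSAs: 15 × 340/102 = 50.

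**The case against.** The strongest reply has five parts.

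- **The outcome is perceptions, from two sources.** It is defined as barriers perceived by HSAs as well as caregivers. Fifteen HSAs would have made about 50 study referrals between them, and caregivers who were never referred can still speak about distance, cost and trust. This stands. A reader might infer that the objective cannot be answered at all, and the documents do not support that. The limit is that HSAs are poorly placed to report caregivers' mistrust of HSA decisions, which the Background lists among the causes of non-completion.
- **A convenience sample is not a random draw.** This stands too. The text does not forbid choosing referred caregivers; it only fails to require it. A reader might take one in 25 as a figure that the plan fixes, but it is an expectation under unselected sampling. The departure could also go the other way: convenience sampling tends to favour people who are easy to reach, and the Sample size section concedes that those referred who did not present are hard to identify.
- **Theoretical sampling is a different matter.** What the article calls impractical is sampling steered by ongoing analysis. Choosing referred caregivers from the start is not ruled out, so that paragraph is not evidence against it.
- **The interviews have a second purpose.** App acceptability needs no referred child, and the Sample size section allows for heterogeneity among interviewees. It does not claim that every caregiver must have faced a referral. Some non-referred interviewees are therefore appropriate.
- **The article is condensed.** A fuller qualitative sampling plan may exist. That would excuse silence, but the article is not silent: it states a frame, and that frame does not serve the objective.

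**Conclusion.** The point holds in a limited form. The stated frame does not ensure that interviewed caregivers had ever faced an urgent referral. If they resemble enrolment, about 1 of 25 had (34% chance of none), about 2 if all came from the intervention phase, and about 0.5 were referred and did not complete (58% chance of none). These figures rest on the plan's assumed referral rates, on unselected sampling, and on 50% non-completion taken from the Background. First-hand caregiver evidence on compliance would then be weak, though not absent, because the HSA interviews and hypothetical views still contribute. The weakness lies in a main objective that is served by an exploratory component. It does not touch the primary outcome.

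**What to change.** Keep 25 caregiver interviews and change the frame.

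- Draw most interviewees purposively from caregivers whose child was urgently referred at the index visit. The village clinic register already records that decision, and about 340 are expected.
- Aim for both completed and uncompleted referrals, and for both phases where available, across the trial as a whole. Doing this within each cluster is not workable: 2 × 2 × 6 = 24 cells for 25 interviews. In control only about 40 × 0.5 = 20 non-completers are expected, roughly 3 per cluster.
- Reserve a small stated share for non-referred caregivers from the intervention phase, for App acceptability.
- Report how many interviewees were urgently referred and how many completed, and limit the triangulation with the primary outcomes accordingly.

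The cost is some tracing of non-completers and slightly later interviews, since completion is established only by the two-week contact and record abstraction. The number of interviews does not change. The article describes the interviews as already held. If so, the reporting step is what can still be done, together with a statement of whether interviewees were in fact chosen by referral and completion status.
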